### 10.5 Informed consent process

The researcher explained the study objectives, procedures, and participants' rights. Informed consent forms were then obtained from the participants, with parental or spousal consent required for those under 18.

### 10.6 Instrument

#### 10.6.1 Instruments for implementation

1. **The parental enhancing program**, developed by the researcher, is based on Belsky's "A Process Model of Competent Parental Functioning". The program consists of the following activities:

- Session 1 (24-48 hours postpartum): Establishes rapport and strengthens the mother-infant bond. The researcher provides personalized knowledge and skills training on recognizing infant cues and responsiveness, general infant care, breastfeeding techniques, bathing procedures, and identifying abnormal symptoms in infants, lasting about 60 to 90

minutes. Teaching materials, such as infographics, e-books, and instructional videos, are disseminated through the 'Line Official Account™ Parent Paplearn' as a mobile application.

- Session 2 (48-72 hours postpartum): Review the previously covered knowledge and offer additional skills training aimed at enhancing the mother's confidence. Individualized support is provided to address her specific concerns, lasting about 60 minutes.

- Session 3 (Post-discharge follow-up): Following discharge, the program includes weekly follow-up messages sent via mobile application through the 'Line Official Account™ Parent Paplearn' for five weeks to address any questions or concerns related to challenges faced by the mother or her infant.

2. **The Line Official Account™ Parent Paplearn** is a mobile application that facilitates the exchange of text messages, images, and videos on a broad scale. This platform also provides a private channel for adolescent postpartum women, enabling them to send messages for consultations or discussions regarding their parenting concerns. The platform is an online tool designed to enable users to create accounts, customize application designs, manage content, and perform system administration functions. The content available on 'Line Official Account™ Parent Paplearn' encompasses essential topics such as recognizing infant cues and responsiveness, general infant care, breastfeeding practices, bathing techniques, and identifying abnormal symptoms in infants. This information is delivered through engaging formats, including infographics, e-books, and videos, designed to enhance understanding and retention among adolescent mothers. The researchers developed the application interface, developed content, and primarily managed the system to address questions from adolescent postpartum women. Participants can review the knowledge as needed, without any limitation on the number of times.

#### 10.6.2 Questionnaire or Assessment form

1. **The demographic characteristics questionnaire** collects data on the mother's age, marital status, education level, occupation, household income (THB), sufficiency of income, family structure, desire for children, plan for future education, childcare support, experience in childcare, number of pregnancies, type of delivery, and the infant's APGAR score.

2. **The postpartum problem and advice record** was developed by the researcher to systematically document follow-up interactions via mobile application through the 'Line Official Account™ Parent Paplearn' after hospital discharge, recording the date, problem, and advice provided.

3. **The Edinburgh Postnatal Depression Scale (EPDS)** was translated into Thai by Vacharaporn et al (2003). This screening tool consists of 10 items. For example, I have been

able to laugh and see the funny side of things, I have looked forward with enjoyment to things, etc. The total scores range from 0 to 30 points. A cut-off score of 11 or higher indicates potential depression. The EPDS serves as an important instrument in assessing the mental health needs of this population, facilitating timely interventions to promote overall well-being.

4. **The Parenting Stress Index Fourth Edition Short Form (PSI-4-SF)** utilized in this study employed the Thai version developed by Srikosa et al (2020). Originally 36 items, it was reduced to 15 to align with the context of the research, specifically focusing on infants aged six weeks postpartum. It measures three domains including 1) Parental distress, 2) Parent-child dysfunctional interaction, and 3) Difficult child, utilizing a five-point Likert scale. Scores range from 15 to 75 points, where lower scores indicate lower levels of parenting stress, while higher scores reflect greater parenting stress.

5. **The Parenting Sense of Competence Scale (PSOC)** was translated into Thai by Kleebran et al (2019). This scale consists of 16 items measuring parenting efficacy and satisfaction. For example, the problems of taking care of a child are easy to solve once you know how your actions affect your child, an understanding you have acquired, etc. Scores ranged from 16 to 96 points. In this context, lower scores indicate lower levels of parenting competence, while higher scores reflect greater competence in parenting.

### **Instrument Quality Assessment**

#### **1. Validity**

The research instruments were reviewed by three experts: two nursing professors specializing in maternal, infant, and obstetric nursing, and one nurse specialist in postpartum care. They evaluated the instruments for content accuracy, appropriate language, use of illustrations, alignment with the study objectives, and content comprehensiveness. The CVI scores for each instrument were as follows:

Line Official Account "Parent Paplearn": CVI = 1.00

The demographic characteristics questionnaire: CVI = 0.93

The postpartum problem and advice record: CVI = 1.00

The Edinburgh Postnatal Depression Scale (EPDS): CVI = 0.70

The Parenting Stress Index Fourth Edition Short Form (PSI-4-SF): CVI = 0.94

The Parenting Sense of Competence Scale (PSOC): CVI = 0.81

#### **2. Reliability**

The researcher tested the Line Official Account "Parent Paplearn", the Parenting Stress Index Fourth Edition Short Form (PSI-4-SF), and the Parenting Sense of Competence Scale (PSOC) with 30 postpartum adolescent mothers whose characteristics closely matched the study

sample. This testing was conducted at Queen Savang Vadhana Memorial Hospital, Thai Red Cross Society, Thailand, following approval from the Ethics Committee. Reliability was then determined using Cronbach's alpha coefficient.

## **11. Data Collection**

### **11.1 Participant Recruitment**

The researcher collaborated with nurses to identify eligible participants who met inclusion criteria and obtained permission to meet them after 24 hours postpartum. During these meetings, the researcher explained the study objectives, procedures, and participants' rights. Informed consent forms were then obtained from the participants.

### **11.2 Data Collection**

1. The research proposal was submitted to the Ethics Committee of Queen Savang Vadhana Memorial Hospital, Thai Red Cross Society, to obtain permission for data collection.

2. Upon approval, the researcher submitted a formal request to the hospital director, which was forwarded to the Nursing Department and relevant ward supervisors to secure permission for data collection.

3. After receiving permission, the researcher introduced themselves to the ward supervisors, explained the study details, and requested cooperation in data collection.

4. The researcher collaborated with nurses to identify eligible participants who met inclusion criteria and obtained permission to meet them after 24 hours postpartum. During these meetings, the researcher explained the study objectives, procedures, and participants' rights. The nurses obtained consent from potential participants to allow the researcher to meet them. The sampling procedure for each group (Figure 3).

[figure not shown]

**Figure 3.** Flow diagram of study.

## **12. Data analysis and statistics**

IBM SPSS Statistics was used for data analysis, statistical significance was set at  $p < .05$ .

1. Descriptive statistics were used to characterize the participant demographic and obstetric characteristics.

2. The comparison of differences between the characteristics of the intervention group and the control group was conducted using independent t-test, Chi-square test, and Fisher's exact test, based on type of the variables and assumptions of statistical.

3. The dependent t-test was used to determine significant differences in parental stress and competence scores before and after the intervention within each group.

4. The independent t-test was used to determine significant differences in parental stress and competence scores between the intervention group and the control group

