#### 1. Personal psychological resources of parents

1.1 **Age** reflects developmental stages, such as adolescence or adulthood, which indicate an individual’s readiness in physical, psychological, and social aspects. Adult mothers

tend to have better cognitive and problem-solving skills, which enhance their parenting competence (Shrooti et al., 2016).

**1.2 Marital Status** Single mothers bear the full responsibility of child-rearing, which may lead to increased stress and psychological challenges.

**1.3 Economic Status** Mothers with sufficient income tend to feel financially secure, enhancing their perceived parenting competence. In contrast, financial hardship can increase stress and lower parenting efficacy (Shrooti et al., 2016).

**1.4 Educational Level** Higher education improves information processing, problem-solving, and adaptability, contributing to more effective parenting (Shrooti et al., 2016).

**1.5 Parity** Previous childbearing experiences enhance maternal skills. Successful prior parenting experiences support more competent current parenting (Barabach et al., 2017).

**1.6 Physical Health** Chronic illness, complications, or medical conditions may require additional self-care, potentially reducing a mother's capacity to care for her child (Maehara et al., 2016).

**1.7 Pregnancy Readiness** Mothers who are prepared for pregnancy are more likely to engage in prenatal care and effective parenting (Shrooti et al., 2016).

**1.8 Self-Esteem** High self-esteem supports effective coping and adaptation, leading to improved parenting performance (Shrooti et al., 2016).

**1.9 Mental Health** Stress, anxiety, or depression may negatively affect parenting effectiveness (Angle et al., 2015; Shorey et al., 2015).

**1.10 Self-Efficacy** High maternal self-efficacy enhances confidence in parenting abilities, contributing to successful child-rearing practices.

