## 9. Research Design

This study employed a quasi-experimental control group pre-post-test design

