### 10.3 Sample size estimation

The sample size for this study was determined using G\*Power (version 3.1.9.4), the effect size indicated a large effect (Cohen's guidelines), a power of test equal to 0.80, and a significance level set at 0.05. The analysis indicated that a sample size of 26 participants per group. To account for dropouts of 10 percent, the final sample was 30 participants per group. Consequently, the total sample size was established at 60 participants.

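### The planned between-group t-test leaves out determinants of parenting competence that this quasi-experimental study collects, and baseline significance tests with 30 per group cannot stand in for adjustment

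*Protocol*

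**What the plan says.** Section 9 states: "This study employed a quasi-experimental control group pre-post-test design". No readable text describes randomisation. Section 11.2 item 4 refers the sampling procedure for each group to Figure 3, which is not shown.

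The literature review (section 4, part 3, on factors influencing parental functioning) lists maternal age, marital status, economic status, education, parity, pregnancy readiness and social support among the influences on parenting. On parity it says: "Previous childbearing experiences enhance maternal skills".

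The demographic questionnaire in section 10.6.2 collects most of these or a close counterpart: age, marital status, education, income, desire for children, and "childcare support, experience in childcare, number of pregnancies, type of delivery".

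Section 12 uses these variables in two ways. Item 1 describes them. Item 2 compares "differences between the characteristics of the intervention group and the control group was conducted using independent t-test, Chi-square test" and Fisher's exact test, with significance at p < .05. The outcomes are analysed by dependent t-tests within each group (item 3) and an independent t-test between groups (item 4). Neither includes a covariate. No rule says what follows from an item 2 result.

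**The concern.** Where randomisation is not described, variables that influence the outcome and may differ between groups need control in the design or the analysis. The protocol identifies such variables and measures most of them, then names an outcome test that cannot take them into account. Item 4 does not say whether it compares post-intervention scores or changes, but neither form adjusts for characteristics such as marital status or childcare support.

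The item 2 tests do not fill the gap. With 30 per group, a non-significant result is compatible with an imbalance large enough to shift the comparison, and a significant one has no stated consequence. At stake is whether a group difference in stress or competence reflects the programme or a difference in who entered each group.

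**Working it through.** **The plan's own sample size.** Inputs from section 10.3: "the effect size indicated a large effect (Cohen's guidelines"), "a power of test equal to 0.80" and "a significance level set at 0.05". No numerical effect is given, so d = 0.8 is assumed. A two-sided two-sample t-test (noncentral t) then needs 26 per group (power 0.807), matching "a sample size of 26 participants per group". A one-sided test would need 21, so the plan is two-sided. For 10% dropout, 26/0.9 = 28.9, or 29; the stated 30 is close. The sample size is not in dispute.

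**What the item 2 tests can detect.** With n per group, the noncentrality is d × √(n/2) on 2n − 2 degrees of freedom.

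| True imbalance (assumed) | Power, 30 per group | Power, 26 per group |
|---|---|---|
| 0.3 SD | 21% | 19% |
| 0.5 SD | 48% | 42% |
| 0.8 SD | 86% | 81% |

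At 30 per group, an observed difference is non-significant below t(0.975; 58) × √(2/30) = 2.002 × 0.258 = 0.52 SD. Power of 80% needs a true difference of 0.74 SD. For a binary characteristic at 20% versus 40%, exact enumeration gives 39% power for chi-square and 30% for Fisher's exact test.

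**Carry-over to the outcome.** Bias in SD units = imbalance × correlation of the characteristic with the outcome. With no true effect, the type I error of the item 4 t-test is its power at d = bias. The documents give neither imbalances nor correlations, so a range is shown for 0.5 SD and 30 per group.

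| Assumed correlation | Bias | Share of d = 0.8 | Type I error |
|---|---|---|---|
| 0.3 | 0.5 × 0.3 = 0.15 SD | 19% | 8.8% |
| 0.5 | 0.5 × 0.5 = 0.25 SD | 31% | 15.9% |
| 0.7 | 0.5 × 0.7 = 0.35 SD | 44% | 26.6% |

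**When the baseline test is non-significant.** In a simulation (40,000 runs, 30 per group, no true effect, correlation 0.5):

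- Imbalance 0.5 SD: the baseline test was non-significant in 52% of runs. Among those, mean bias was 0.15 SD and type I error 7.1%.
- Imbalance 0.3 SD: it was non-significant in 79% of runs. Among those, mean bias was 0.10 SD and type I error 5.6%.

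**With adjustment.** In the same simulation, ANCOVA on the confounder gave a bias of about 0.00 SD. Type I error fell from 16.0% to 5.0% (0.5 SD) and from 9.0% to 5.1% (0.3 SD).

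**The case against.** The strongest objection is that group formation cannot be seen. Figure 3 may show matching or another control of comparability. That stands as a limit: no readable text mentions matching, but its absence is not established.

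Second, eligibility already narrows some factors. Section 10.4 limits the sample to ages 15 to 19, term delivery, no maternal complications and no infant separation. This reduces the scope for confounding by age and health. It does not restrict number of pregnancies, childcare experience, marital status or support.

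Third, covariate lists are often left to a statistical analysis plan. That would answer a complaint about missing detail, but item 4 names the between-group test for both outcomes, and adjustment would have to replace it.

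Fourth, the bias that survives a non-significant test is modest for one confounder: 0.15 SD and 7.1% in the scenario above. That is correct; several confounders acting in one direction would add up.

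A reader might infer that the report will call the groups comparable because p exceeded .05, or that a significant imbalance will be ignored. The protocol says neither. It gives no decision rule, and item 1 would let readers see imbalances directly.

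**Conclusion.** The point holds in limited form. For a quasi-experimental comparison the protocol fixes an unadjusted between-group t-test, while its stated use of the collected determinants stops at description and significance tests. Those tests can miss material imbalance, so measured confounding can remain in the estimates for both outcomes.

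The size is conditional. Under an assumed 0.5 SD imbalance and correlations of 0.3 to 0.7, the bias is 0.15 to 0.35 SD. The power figures are firm, but the imbalances and correlations are assumptions. The documents do not support saying that the groups are in fact imbalanced, or that a 16% error rate applies to this study. The case for change rests on a stated method having a better alternative at little cost.

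**What to change.** Replace section 12 item 4 with an ANCOVA of each post-intervention score (PSI-4-SF and PSOC) on group, the pre-test score of the same scale, and a short covariate list fixed in advance. The list should come from variables that section 10.6.2 collects and the literature review supports, for example maternal age, number of pregnancies, marital status and childcare support. Number of pregnancies is the collected counterpart of parity, which the questionnaire does not list. Use the covariates whatever item 2 shows, and state that its p-values do not decide on adjustment.

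Standardised differences may be reported descriptively, but without a flag at 0.1 or 0.2. With 30 per group their standard error is about √(2/30) = 0.26, so balanced populations would exceed 0.1 about 70% of the time and 0.2 about 44%.

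**Cost.** No new data are needed. Five one-degree-of-freedom covariates use 5 of 58 degrees of freedom (50 at 26 per group). If they are useless, the standard error grows by about √(58/53) = 1.046 to √(50/45) = 1.054, roughly 5%. It grows somewhat more if they are imbalanced: about 8% at 30 per group with one covariate 0.5 SD apart. A useful covariate more than repays this. At d = 0.8 and 26 per group, one correlating 0.5 with the outcome raises power from 0.81 to about 0.90, ignoring the small loss from imbalance. Unmeasured confounding remains and should be stated as a limitation.

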## **2. Concept of the Maternal Role**

### **2.1 Theory of Maternal Role**

Rubin (1975) developed the Theory of Maternal Identity, which involves the following processes:

Replication: Women mimic or model their maternal behavior after their own mothers or other maternal figures.

Fantasy: Women imagine how they will perform their maternal role and how they will care for their child in the future.

Dedifferentiation: Women learn the maternal role by seeking role models among close individuals, then choose a model that fits them or reject roles they find unsuitable.

Identity Formation: Women establish a maternal identity by adopting a role that suits them, accepting their new role, expressing satisfaction, and effectively fulfilling maternal responsibilities.

In 1985, Mercer expanded on Rubin's concept, describing maternal role development as a continuous and dynamic process from pregnancy through postpartum, consisting of four stages (Mercer, 2004):

1. **Commitment, Attachment, and Preparation** This stage occurs during pregnancy, where women prepare for motherhood by caring for their health, seeking information on pregnancy care, developing an attachment to the fetus, and learning about the maternal role.

2. **Acquaintance, Learning, and Physical Restoration** Starting from childbirth until six weeks postpartum, women begin to enact the maternal role according to advice and expectations from others.

3. **Moving Toward a New Normal** From two weeks to four months postpartum, mothers increasingly express their maternal role in a way that reflects their own characteristics, based on experience and learning.

4. **Achievement of Maternal Identity** After four months postpartum, mothers gain confidence, competence in child-rearing, and satisfaction in fulfilling their maternal role.

Successful maternal role attainment can be evaluated by three components: 1) attachment to child, 2) confidence/ competence in role, and 3) gratification/ satisfaction.

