## 7. Research hypothesis

1. Participants in the intervention group experienced significantly lower levels of parental stress compared to those in the control group.
2. Participants in the intervention group experienced significantly higher scores in parental competence compared to those in the control group.

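### Within-group pre-post t-tests stand level with the between-group test yet answer neither hypothesis; make them descriptive and judge both hypotheses on one between-group contrast adjusted for the pre-test

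*Protocol*

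**What the plan says.** Protocol section 12 sets one significance level, p < .05, for all analyses and then lists four items. Item 1 is labelled descriptive and item 2 compares group characteristics. The outcome analyses are:

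- Item 3: "The dependent t-test was used to determine significant differences in parental stress and competence scores before and after the intervention within each group".
- Item 4: "The independent t-test was used to determine significant differences in parental stress and competence scores between the intervention group and the control group".

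Items 3 and 4 are worded alike. Neither is called primary or supportive. Item 4 does not say whether the scores compared are post-test scores or changes.

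Section 7 states both hypotheses as comparisons with controls; the second reads "Participants in the intervention group experienced significantly higher scores in parental competence compared to those in the control group". Objectives 2 and 3 in section 5 likewise compare program participants with mothers under standard care. No objective or hypothesis concerns change within a group.

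Section 9 describes a quasi-experimental two-group design with a pre-test and a post-test. Section 10.3 plans 26 per group, raised to 30 for dropout.

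**The concern.** A paired test within one group asks whether scores moved, not whether the program moved them. Controls receive standard care, so their test can show only change without the program. In the intervention group the same test picks up that change plus any program effect and cannot separate the two.

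The protocol gives some reason to expect scores to move in both groups. Its account of maternal role theory says: "Starting from childbirth until six weeks postpartum, women begin to enact the maternal role".

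Because item 4 does not mention the pre-test, item 3 is the only outcome analysis that explicitly uses it. A reader looking for improvement will therefore turn to the two within-group p-values. A significant change in one group beside a non-significant change in the other is not a test of the difference between groups. It can disagree with item 4, and the plan does not say which result prevails.

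**Working it through.** **Inputs.** From the protocol: 26 per group before dropout and 30 after; two outcomes; "a significance level set at 0.05" and "a power of test equal to 0.80" (section 10.3); p < .05 in section 12. The effect size is given only in words: "the effect size indicated a large effect (Cohen's guidelines". Assumed: d = 0.8 for a large effect; two-sided tests; independent groups; the same natural change in both groups; pre-post correlation 0.5 in the simulation. The documents give no natural change, so a range is shown.

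**Step 1: the plan's own figure.** A two-sample t-test with d = 0.8, two-sided alpha 0.05 and power 0.80 needs 26 per group by the noncentral t distribution (power 0.807). Dropout: 26 / 0.90 = 28.9, so 29; the stated 30 is one more. The sample size therefore fits the between-group test in item 4.

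**Step 2: false pattern from two paired tests.** Let dz be the common natural improvement in units of the SD of change, with no program effect. The chance that one group shows a significant improvement is

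p = P(T > t(0.975, n−1)), with T noncentral t on n−1 degrees of freedom and noncentrality dz × √n.

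The groups are independent, so the chance that the intervention group is significant and the control group is not is p × (1 − p). This cannot exceed 0.5 × 0.5 = 25%.

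| dz | p, n = 30 | intervention only, n = 30 | intervention only, n = 26 |
|---|---|---|---|
| 0 | 2.5% | 2.4% | 2.4% |
| 0.1 | 7.6% | 7.1% | 6.6% |
| 0.2 | 18.4% | 15.0% | 13.7% |
| 0.3 | 35.5% | 22.9% | 21.5% |
| 0.36 | 47.9% | 25.0% | 24.4% |
| 0.4 | 56.3% | 24.6% | 25.0% |
| 0.5 | 75.4% | 18.6% | 21.5% |
| 0.6 | 88.8% | 9.9% | 13.7% |
| 0.8 | 98.8% | 1.1% | 2.4% |
| 1.0 | over 99.9% | under 0.1% | 0.2% |

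For example, at dz = 0.36 and n = 30: 0.479 × 0.521 = 0.250.

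The second column shows a separate hazard. When natural change is large, the one-group-only pattern disappears, but the intervention group's own paired test is almost always significant: 98.8% at dz = 0.8 with no program effect.

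**Step 3: the between-group test under the same conditions.** In 40,000 simulated trials per setting with n = 30, the paired-test pattern occurred in 2.5%, 14.9%, 25.2%, 18.7% and 1.3% of trials at dz = 0, 0.2, 0.36, 0.5 and 0.8, which agrees with the formula. The independent t-test rejected in 4.8% to 5.2% of trials, on post-test or change scores, whatever the natural change. Half of the nominal 5%, that is 2.5%, favours the program. The simulated groups were comparable at baseline.

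**The case against.** The strongest reply is that the right test is already planned. Item 4 compares the groups on both outcomes, matches the hypotheses and is the test for which the sample size works out. Showing within-group change beside it is not an error in itself, and ranking analyses is often left to a statistical analysis plan, which may exist. Much of this stands and limits the point. It does not remove it, because this protocol itself fixes item 3 as significance testing at the same level as item 4, and for a question that no hypothesis asks.

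A reader might go further in several ways that the documents do not support:

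- **That the paired tests are planned as efficacy tests.** The protocol does not call them that and has no rule inferring benefit from significance in one group only. Step 2 shows what would follow if someone compared the p-values, not what the plan prescribes.
- **That the false pattern is frequent as a matter of course.** It runs from under 0.1% to 25% per outcome at n = 30, depending on an unknown natural change. Showing only 0.3-0.5 SD would select the values around the peak.
- **That both outcomes naturally improve.** The quoted theory concerns the maternal role, not parenting stress, and places gains in confidence and competence after four months. Section 3 suggests that lack of follow-up after discharge may make anxiety worse. Under a common worsening, a false improvement in the intervention group has a chance below 2.5%. By symmetry, though, the pattern of controls significantly worse and the intervention group not has the same p × (1 − p).
- **That regression to the mean contributes.** The entry criteria in section 10.4 set no stress or competence threshold, so they do not select extreme scores.
- **That the tests span exactly six weeks.** This is an inference from the follow-up schedule and the shortened stress scale; the readable text does not date the two assessments.

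**Conclusion.** The point holds in a limited form. Section 12 gives four paired tests the same inferential standing as the between-group test, although they answer neither hypothesis and cannot separate natural change from a program effect. The protocol neither says that conclusions rest on item 4 alone nor that item 4 uses the pre-test.

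The risk is conditional: it arises if the within-group p-values are compared, or if the intervention group's p-value is read alone. For the first misuse, the table gives a rate well above the between-group test's 2.5% only for a natural change of roughly 0.1-0.6 SD of change. These figures assume equal natural change in both groups and two-sided tests. The 2.5% also needs groups comparable at baseline, which a quasi-experimental design does not guarantee. The defect is worth correcting because the correction is cheap, but it does not mean that the trial lacks a between-group test.

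**What to change.** In section 12, item 3, replace the paired significance tests with the mean change and its 95% confidence interval for each outcome in each group, labelled descriptive only.

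In item 4, state that both hypotheses are judged only on the between-group difference in post-test score adjusted for the pre-test score (ANCOVA), reported with its 95% confidence interval.

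The cost is a few sentences in section 12. The pre-test is already part of the design, no new data are needed, and four tests drop out. Adjustment for the pre-test deals with imbalance in that score only; other differences between non-randomised groups remain a separate matter. If the analysis has already been run, the same change can be made in the report and declared as a change to the plan.

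### The only between-group test ignores the pre-test score, although the groups are not randomised

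*Protocol*

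**What the plan says.** Protocol section 9 describes the design: "This study employed a quasi-experimental control group pre-post-test design". No readable text describes randomisation. Both hypotheses in section 7 compare the two groups; the first reads "Participants in the intervention group experienced significantly lower levels of parental stress compared to those in the control group", and the second makes the corresponding claim for competence. Objectives 2 and 3 in section 5 are also between-group comparisons.

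Section 12 holds three relevant steps:

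- Item 2 checks comparability: "The comparison of differences between the characteristics of the intervention group and the control group was conducted using independent t-test", with chi-square and Fisher's exact tests for other variable types. It gives no consequence if a difference is found.
- Item 3 uses the pre-test scores: "The dependent t-test was used to determine significant differences in parental stress and competence scores before and after the intervention within each group".
- Item 4 is the between-group test: "The independent t-test was used to determine significant differences in parental stress and competence scores between the intervention group and the control group". It names no covariate, does not say whether the score is post-test or change, and gives no time point.

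The protocol contains no ANCOVA, regression, matching or other adjustment.

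**The concern.** Item 4 is the only analysis that answers the hypotheses, because paired tests within each group cannot show a difference between groups. In a non-randomised study the groups may differ at the start. The protocol's own literature review (section 4, on factors influencing parental functioning) lists age, marital status, income, education, parity, mental health, social support and infant temperament as influences on competence. An unadjusted post-test comparison mixes any such starting difference with the program effect, in either direction. The pre-test of the same outcome measures part of that difference directly, is already collected, and is left out of the comparison. The variance it explains also stays in the error term, in a study of 60 mothers.

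**Working it through.** **Inputs from the protocol (section 10.3).** The effect size is described only in words: "the effect size indicated a large effect (Cohen's guidelines". Power and alpha are given as "a power of test equal to 0.80, and a significance level set at 0.05". The result is "The analysis indicated that a sample size of 26 participants per group", raised to 30 per group for 10% dropout.

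**Assumptions, not in the protocol.** d = 0.8 for a large effect; two-sided test; pre/post correlation r = 0.3, 0.5 or 0.7; true baseline difference D = 0.3 or 0.5 SD; equal variances and a common slope in both groups.

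**Step 1: reproduce the planned size.** For a two-sample t-test, the noncentrality is d × √(n/2) with 2n − 2 degrees of freedom. Solving for power 0.80 at d = 0.8 gives n = 25.5, rounded up to 26. With n = 26 the noncentrality is 0.8 × √13 = 2.88 and power is 0.807. A one-sided test would need 21. The planned size therefore matches an unadjusted two-sided t-test at d = 0.8.

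**Step 2: bias of the unadjusted post-test comparison.** With no program effect, the expected post-test difference is r × D. The false-rejection rate uses noncentrality r × D × √(n/2), with n = 30 and 58 degrees of freedom.

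| D (SD) | r | Bias (SD) | Share of d = 0.8 | Rejection rate at nominal 5% |
|---|---|---|---|---|
| 0.3 | 0.3 | 0.09 | 11% | 6.4% |
| 0.3 | 0.5 | 0.15 | 19% | 8.8% |
| 0.3 | 0.7 | 0.21 | 26% | 12.6% |
| 0.5 | 0.3 | 0.15 | 19% | 8.8% |
| 0.5 | 0.5 | 0.25 | 31% | 15.9% |
| 0.5 | 0.7 | 0.35 | 44% | 26.6% |

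With 26 per group the rates are slightly lower: 8.3% for D = 0.3 and r = 0.5, and 23.6% for D = 0.5 and r = 0.7.

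**Step 3: does item 2 protect against this?** A two-sided 5% t-test on a baseline variable with 26 to 30 per group detects a 0.3 SD difference with power 0.19 to 0.21, and a 0.5 SD difference with power 0.42 to 0.48. Imbalances of the size in the table would more often be missed than found.

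**Step 4: power with the pre-test as covariate.** ANCOVA reduces the residual variance by the factor 1 − r², so the noncentrality becomes d/√(1 − r²) × √(n/2), with 2n − 3 degrees of freedom. Imbalance inflates the variance of the adjusted difference by about 1 + D²/4. With d = 0.8 and n = 26:

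| r | Unadjusted t-test | ANCOVA, D = 0 | ANCOVA, D = 0.3 | ANCOVA, D = 0.5 |
|---|---|---|---|---|
| 0.3 | 0.807 | 0.842 | 0.834 | 0.820 |
| 0.5 | 0.807 | 0.904 | 0.898 | 0.886 |
| 0.7 | 0.807 | 0.977 | 0.975 | 0.970 |

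**The case against.** **Which score is tested.** Item 4 says only scores. If it meant change scores, the raw baseline difference would be subtracted and the bias in step 2 would not apply. The post-test reading is natural but is an inference. A change-score test would still be open to regression to the mean, and its variance factor 2(1 − r) exceeds 1 when r is below 0.5, so it is then less precise than the post-test alone. On either reading item 4 has to be rewritten.

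**How groups were formed.** Section 11.2 refers the sampling procedure for each group to Figure 3, which is not reproduced in the text at hand. Matching or another balancing step cannot be ruled out. The protocol's own label remains quasi-experimental, and no analysis reflects such a step.

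**Low correlation is plausible.** Recruitment takes place after 24 hours postpartum (section 11.1), and section 10.6.2 says the stress scale was shortened with six-week-old infants in mind. At r = 0.1 to 0.2, a 0.3 SD imbalance gives a rejection rate of only 5.1% to 5.6%, and ANCOVA with balanced groups has power 0.81 to 0.82. The power argument is therefore weak at the low end: at r = 0.3 with imbalance allowed for, the gain is 0.01 to 0.03. This stands, and the case rests mainly on bias.

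**ANCOVA is a partial remedy.** It adjusts for the measured pre-test score only. Confounding through childcare experience, childcare support or income, all recorded under section 10.6.2, can remain. This also stands, but it does not justify leaving out the most directly relevant baseline variable.

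**The statistical analysis plan might add adjustment.** The protocol names the test, so this is a stated choice and not a gap left for later.

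**Conclusion.** The concern holds and must be fixed. A non-randomised pre/post design is paired with an unadjusted t-test as the sole test of both hypotheses, while the pre-test scores are collected and not used between groups. A positive result could not be separated from a difference present at the start. Over r = 0.3 to 0.7, the bias is 11% to 26% of d = 0.8 for a 0.3 SD imbalance and 19% to 44% for 0.5 SD, with false rejection of 6% to 13% and 9% to 27% at 30 per group. These figures depend on an assumed r, assumed imbalances, d = 0.8 read from a verbal description, and the post-test reading of item 4. The direction of the argument holds for any positive r. The loss of power is real for r of about 0.5 or more and minor below that.

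**What to change.** Replace item 4 of section 12 with text such as: *The primary analysis for each outcome is ANCOVA of the six-week score on group, with the pre-test score of that outcome as covariate. The adjusted mean difference, with its 95% confidence interval and two-sided p-value, is the test of each hypothesis.* Keep the unadjusted t-test as a supporting analysis, with its score and time point named. State that adjustment for the pre-test does not remove confounding by other characteristics.

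The cost is a short text change and one degree of freedom per outcome. No new data are needed and SPSS runs the model. Section 12 is written in the past tense and the timeline ends in December 2023; if outcome data have already been analysed, the change should be declared as made after the fact and both results reported.
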